#### sncRNA (miRNA) expression analysis

The sncRNA targets from saliva will be extracted using the MagMAX mirVana total RNA isolation kit (A27828, Thermo Fisher Scientific, Waltham, Massachusetts, US) using manufacturer’s instruction with modification for saliva extraction. After isolation of total RNA (including snc/miRNA), these will undergo polyadenylation, adapter ligation, reverse-transcription and miR-Amp reactions using the TaqMan™ Advanced miRNA cDNA Synthesis Kit (A28007, Thermo Fisher Scientific, Waltham, Massachusetts, US) following manufacturer’s instructions. Reactions will be performed on the standard thermocycler BioRad. The cDNA will be diluted, and real-time PCR runs for miRNA analysis will be performed using the Taqman Fast Advanced Mastermix for qPCR (4,444,964, Thermo Fisher Scientific, Waltham, Massachusetts, US) on QuantStudio™ 7 Flex Real-Time PCR System (Thermo Fisher Scientific, Waltham, Massachusetts, US).

Using TaqMan® Assays for miR-27a-5p and miR-30a-3p (assays 002445 and 000416 respectively, Thermo Fisher Scientific, Waltham, Massachusetts, US) their respective expressions will be calculated by the 2^−ΔΔCt^ method by using endogenous miRNA, one of RNU48, RNU44, U47, or RNU6B (Thermo Fisher Scientific, Waltham, Massachusetts, US) will be used as the reference genes. The ratio of miR-27a-5p/miR-30a-3p expression will be calculated. The ratio of these two miRNAs has previously been reported to differentiate concussed and non-concussed individuals; concentrations of miR-27a-5p and miR-30a-3p differentiated 75 concussed individuals from 97 non-concussed individuals with 82.4% sensitivity and 73.3% specificity. The levels of miR-27a-5p/miR-30a-3p were lower among concussed individuals and importantly showed no effect of acute or chronic exercise. These miRNAs showed similar accuracy for both sport and non-sport related concussion.

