Participants are categorised into one of five hormone profiles as follows; 1) Follicular phase if question C1 is answered as “1 week ago”, 2) Mid-cycle if question C1 is answered “2 weeks ago”, 3) Luteal phase if question C1 is answered “3 weeks ago” or “4 weeks ago”, 4) Oligomenorrheic if C1 was answered “1–2 months ago”, “3–4 months ago” or “5 months ago or more”, 5) Using contraceptive if question 3.1a is answered “yes”.

Scoring of question 3.2 remains the same, i.e., if a participant ticks any of the boxes within the 0–4 weeks’ timeframe the same score is applied as the original question. In eumenorrheic participants this will help estimate menstrual cycle phase at point of injury. This information is used to understand any association between hormonal profile and or LEAF_Q score with symptom severity and duration of concussion.

The Brain Injury Screening Tool (BIST) is a brief screening tool for use on initial presentation after injury to guide health care pathway decision making and to monitor symptoms and recovery over time. [59] The BIST was developed in the NZ context to fit the clinical environment and to provide consistency across multiple environments and referral pathways (e.g. GP clinic, ED, Urgent Care Centres), the tool has also been psychometrically tested. There are two sections in the BIST; the first section is used to determine if there are any clinical ‘red flags’ which require referral to hospital, therefore this component is not included in this study. The second section of the BIST includes a 16-item symptom report scale for patients to rate how much they now experience the symptoms listed on a scale of 0 (not at all) to 10 (severe). Higher symptom scores are indicative of higher symptom burden. Participants are asked to complete this part of the BIST at point of presentation with injury and at seven-day time intervals throughout the study to monitor symptoms and recovery over time.

The final question asks if the participant has made a full return to work/study and how many follow-up appointments they had. The number of days between injury and full return to work/study will be used as a proxy for recovery. This question is included in the weblink sent at all timepoints (i.e., 7, 14, 21, 28 days etc.) until the participant reports they have achieved a full return to work/study, at which point participation in the study will be complete. Detail of information collected each week is included in Table 2.

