## Data analysis

In this study a range of statistical tests will be used to analyse the data corresponding to the four aims. Aim 1 will use Cox proportional hazards regression to determine if the time to recovery from concussion (measured in days), differs among groups categorised by hormone profile at the point of injury (five profiles: Follicular phase, Midcycle, Luteal phase, oral contraception, IUD). Aim 2 will apply an ANOVA to compare the ratios of miR-27a-5p/miR-30a-3p expression, across these five groups. Model-estimated means and pairwise contrasts between groups will also be computed. For Aim 3, the focus is on whether self-reported symptoms, quantified both as the number of symptoms present (range 0–16) and as a total symptom burden (sum of severity scores; range 0–160), differ among hormone profile categories. These dependent variables will be analysed using ANOVA, with the five hormone profiles specified as the independent variable. Aim 4 will employ a linear mixed model to investigate changes in low energy availability across the recovery period. This model will incorporate the day of recovery and total symptom burden as fixed effects and will account for repeated measures over time by specifying participant as a random effect. The interaction between symptom burden and recovery time will also be evaluated to understand if these variables are collectively associated with low energy availability.

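### Aim 3 gives a weekly repeated symptom score an ANOVA with no occasion, time or participant term, and Aim 2 would be better analysed as a log2 ratio; both are cheap to improve

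*Protocol article*

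**What the plan says.** **Aim 3.** Symptoms are "quantified both as the number of symptoms present (range 0–16) and as a total symptom burden (sum of severity scores; range 0–160". The model is: "These dependent variables will be analysed using ANOVA, with the five hormone profiles specified as the independent variable" (Data analysis). The schedule is in Surveys and questions: "Participants are asked to complete this part of the BIST at point of presentation with injury and at seven-day time intervals throughout the study". Table 2 agrees, marking the BIST at initial assessment and during recovery. The weekly link continues "until the participant reports they have achieved a full return to work/study, at which point participation in the study will be complete".

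**Aim 4, same paragraph.** A linear mixed model is planned that "will account for repeated measures over time by specifying participant as a random effect".

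**Aim 2.** The laboratory section computes the expression of each miRNA by the 2^−ΔΔCt method, and then "The ratio of miR-27a-5p/miR-30a-3p expression will be calculated". The analysis is: "Aim 2 will apply an ANOVA to compare the ratios of miR-27a-5p/miR-30a-3p expression", followed by model-estimated means and pairwise contrasts. No transformation is mentioned.

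**The concern.** A one-way ANOVA needs one independent observation per woman. The BIST yields several, and their number depends on how fast she recovers, because follow-up ends at return to work or study. The Aim 3 model neither says which observation is used nor has a term that would accommodate all of them. What is at stake is an occasion left open for two outcomes, unused recovery data or, if every record were entered, standard errors that are too small and extra weight for slow recoverers.

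For Aim 2, each expression is 2 raised to a difference in cycle thresholds. If those thresholds are roughly normal, the ratio is right-skewed and a few large values can dominate group means and the error variance. With 30 to 38 women in five groups (30/5 = 6; 38/5 = 7.6), there is little power to spare.

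**Working it through.** **The plan's own figure.** The only sample size is for Aim 1, and it reproduces. N = (z₀.₉₇₅ + z₀.₈₀)² / [event rate × (1 − R²) × SD² × (log HR)²] = 7.849 / (0.9 × 0.8 × 2.25 × 0.4055²) = 7.849 / 0.2664 = 29.5, rounded up to 30. With 20% dropout, 30/0.8 = 37.5, rounded up to 38. Aims 2 and 3 have no stated power.

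**Aim 3: the two readings.**

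*(a) One record per woman.* Simulated type I error of the one-way ANOVA (30 women, five groups) is 0.050, so it is valid.

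*(b) All records entered.* Null simulation with 20,000 replicates, 30 women in five groups of 6 and nominal level 0.05. The number of records and the within-person correlation are assumptions, because the protocol gives neither.

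| Records per woman | r = 0.3 | r = 0.5 | r = 0.7 |
|---|---|---|---|
| 2 | 0.12 | 0.19 | 0.26 |
| 4 | 0.30 | 0.45 | 0.58 |
| 6 | 0.45 | 0.63 | 0.75 |

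Results for 38 women are almost the same. The table gives every woman the same number of records. In practice a woman returning at week 6 would supply 1 + 6 = 7 rows and one returning at week 1 would supply 1 + 1 = 2, a weight of 7/2 = 3.5 to 1 towards slow recovery.

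**Aim 2: the natural scale.** Let ΔΔCt = (Ct target − Ct reference) in the sample minus the same difference in the calibrator. With the same reference gene for both targets:

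log2(ratio) = −ΔΔCt(27a) + ΔΔCt(30a) = [Ct(30a) − Ct(27a)] in the sample − [Ct(30a) − Ct(27a)] in the calibrator.

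The reference gene cancels and the calibrator term is a constant, so the log2 ratio is a plain Ct difference.

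**Aim 2: skewness and power.** Assume that this difference is normal with SD s cycles; the documents give no SD. The raw ratio then has skewness (e^v + 2)√(e^v − 1), with v = (s × ln 2)². The power simulation uses five groups of 7 and one group shifted by 1.5 SD on log2. Type I error is from the run with five groups of 6.

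| Log2 SD | Skewness of ratio | Raw type I error | Power, one group lower: raw | Power, one group higher: raw | Power, log2 (either direction) |
|---|---|---|---|---|---|
| 0.5 | 1.1 | 0.047 | 59% | 78% | 75% |
| 1.0 | 2.8 | 0.041 | 34% | 74% | 75% |
| 1.5 | 6.9 | 0.032 | 17% | 64% | 75% |
| 2.0 | 21.3 | 0.028 | 10% | 52% | 75% |

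Repeat runs differ by about one percentage point. With five groups of 6 the pattern is the same: about 66% logged, against 50% to 9% raw (one group lower) and 71% to 45% raw (one group higher).

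**The case against.** The strongest reply on Aim 3 is that nothing says the weekly scores are pooled. The Aim section gives Aim 3 no time element and reserves the recovery period for Aim 4, which alone gets a mixed model. The authors clearly recognise repeated measures, so a single-occasion Aim 3 is a natural reading, and on it the ANOVA is valid. That stands: a reader might infer that the plan will produce false positives, but the documents do not support this. What remains is that no occasion is named among several scheduled ones, and the planned method leaves the weekly data unused.

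On Aim 2, transformation is often left to an analysis plan, which is not shown here. The skewness and power figures rest on assumed SDs, and the raw-scale test is at worst conservative. All of that stands, so it would be too strong to say that ANOVA does not fit these data. A reader might also infer that power is lost in the direction the protocol expects, because the laboratory section reports a lower ratio in concussed people. That comparison is with non-concussed people. Every participant here has a concussion, and the protocol states no expected direction between hormone profiles. Both directions must therefore be shown; with one group higher and a log2 SD of 1 or less, the raw scale loses essentially nothing.

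**Conclusion.** The point holds as an inexpensive improvement to two secondary analyses, not as a demonstrated error.

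- **Aim 3.** The written model neither fixes a BIST occasion nor accommodates the repeats. The type I error of 0.12–0.75 applies only if all records are entered, under the assumed correlations and record counts. A later single week would be a poor choice, because only women who have not yet returned to work or study are still observed.
- **Aim 2.** The log2 scale follows from how the ratio is built. Its benefit depends on the true SD and on direction: large if one group is lower (75% against 59% to 10%), and from a loss of about 3 points to a gain of about 23 if one group is higher (75% against 78% to 52%). This assumes roughly normal Ct values, equal groups and a 1.5 SD shift. False positives are not the issue.

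**What to change.** **Aim 3.** State that the primary comparison is symptom count and total burden at presentation, by ANOVA across the five profiles. Add a linear mixed model for each outcome over all occasions, with profile, day, profile-by-day and a participant random effect. State that observation ends at recovery, so later weeks describe only women still under follow-up.

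**Aim 2.** Run the ANOVA and pairwise contrasts on the log2 ratio, and back-transform to geometric-mean ratios with confidence intervals.

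**Cost.** A few sentences of analysis wording and slightly more analysis work. No extra data are needed, and a mixed model is already planned for Aim 4. The only statistical downside is a trivial power loss for Aim 2 if the log2 SD is small and one group is higher (75% against 78% at SD 0.5). Recruitment is still in progress, so the change should be recorded before the data are analysed.

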## Methods/design

### Aim

The aims of this study are to: 1) determine if the time to recovery (in days) differs among groups categorised by their hormone profiles at the point of concussion injury, 2) examine whether the ratio of sncRNAs in saliva differ across groups categorised by their hormone profiles at the point of concussion injury, 3) assess whether self-reported symptoms differ among groups categorised by their hormone profiles at the point of concussion injury, and 4) investigate whether low energy availability changes across the recovery period, and if this is associated with symptoms experienced.

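### The only model named for Aim 4 estimates change in low energy availability at fixed symptom burden, not the overall change over recovery that the aim asks about first

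*Protocol article*

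**What the plan says.** The Aim section gives Aim 4 two parts, in this order: "investigate whether low energy availability changes across the recovery period, and if this is associated with symptoms experienced".

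The Data analysis section assigns the change question to one model: "Aim 4 will employ a linear mixed model to investigate changes in low energy availability across the recovery period". Its content is then fixed: "This model will incorporate the day of recovery and total symptom burden as fixed effects", and it "will account for repeated measures over time by specifying participant as a random effect". The text goes on: "The interaction between symptom burden and recovery time will also be evaluated to understand if these variables are collectively associated with low energy availability". No model without burden is described.

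Burden is not a baseline covariate. It is the sum of the 16 BIST severity ratings (0 to 160), collected at presentation and then "at seven-day time intervals throughout the study to monitor symptoms and recovery over time". The LEA questionnaire (LEAF-Q) starts at day 7 and is also weekly, so each LEA score has a burden score from the same week.

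**The concern.** Day is the only time term in the model. Once burden is in the model too, the day coefficient compares records at the same burden. That answers a different question: does LEA change over time beyond what the change in symptoms accounts for? The first half of Aim 4 has no such condition.

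The two quantities agree only if burden does not change over recovery or has no relation to LEA. The BIST is collected to follow recovery, so burden should fall with day, and the second half of the aim exists because a relation to LEA is thought possible. What is at stake is an understated change in LEA over recovery and, in the extreme, a day term that shows none although LEA did change.

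**Working it through.** **Inputs from the protocol article.** The two-part aim (Aim section). Day and burden as joint fixed effects, participant as random effect, and the interaction (Data analysis). Weekly LEAF-Q and BIST (Surveys and questions). 30 evaluable and 38 recruited women (Sample size calculation).

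**The plan's own figure.** No sample size is given for Aim 4. The Aim 1 figure reproduces for a two-sided test:

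- events = (1.960 + 0.842)² / (1.5² × 0.4055² × (1 - 0.2)) = 26.5
- 26.5 / 0.9 = 29.5, rounded up to 30
- 30 / 0.8 = 37.5, rounded up to 38

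The values 30 and 38 are used below.

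**What the day term estimates.** Let LEA = a + u + βB + γt + error, where u is the participant effect, B is burden and t is week. Let B fall by δ per week on average.

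- Overall change per week (day only): γ - βδ
- Day term with burden in the model: γ
- Share of the overall change left in the day term: γ / (γ - βδ)

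The share is 0 if the change runs wholly through symptoms (γ = 0), one half if half of it does, and 1 if burden is unrelated to LEA (β = 0). With an interaction coefficient θ, the slope at burden B is γ + θB, so an uncentred day term is the slope at burden zero, the end of the scale.

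**Simulation, assumed values A.** None of these values is in the documents. Starting burden has mean 50 and SD 15. It falls by 10 per week and is floored at 0, with within-woman SD 5 or 10. There are 4 weekly records (in one setting 2 to 6). β = 0.06 LEAF-Q points per burden point, participant SD 2, residual SD 1.5. Each setting has 200 trials. The first row covers five settings with N = 30 or 38; the other rows have N = 38.

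| LEA change | Day-only slope per week | Day only, significant | Day term with burden | Significant | Day significant, uncentred interaction | Same, burden centred | Burden significant |
|---|---|---|---|---|---|---|---|
| Wholly through symptoms | -0.48 to -0.56 | 99-99.5% | -0.01 to 0.03 | 3.5-6.5% | 3.5-10% | 3.5-7% | 83.5-100% |
| About half through symptoms | -1.03 | 100% | -0.49 | 89.5% | 64% | 87.5% | 100% |
| Unrelated to symptoms | -0.60 | 100% | -0.59 | 96% | 74% | 96% | 5.5% |

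The algebra gives 0 - 0.06 × 10 = -0.6 for the first row; the floor at zero burden brings this to about -0.5. In the second row the share left is 0.487 / 1.032 = 0.47, close to the one half expected. The joint 3-df test of day, burden and interaction rejected in 99.5-100% of trials in every row.

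**Assumed values B.** 38 women, median recovery 14 or 21 days, participant SD 3, residual SD 1.2, β = 0.06, 150 cohorts per scenario. With the change wholly through symptoms, LEA falls by 0.26-0.31 points per week. Day alone detects this in 99-100% of cohorts, and the day term of the planned model is significant in 3-7%. With no change, both reject in about 5-7%, so the advantage of the day-only model is not inflated type I error.

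**Assumed values C.** 38 women who leave at recovery. With the change wholly through symptoms, day is significant in about 8% of cohorts, burden in 93% and the joint test in 100%. With half of the change independent of symptoms, day is significant in 25%.

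**The case against.** The strongest reply is that the plan never makes the day coefficient, read alone, the test of change. Its last sentence on Aim 4 speaks of the two variables collectively, which can be read as a joint assessment, and a joint test rejects almost always when LEA follows falling symptoms. This stands against one tempting inference, that following the plan would lead to a report of no change. That needs a reading rule the article does not contain, as well as a change that runs almost wholly through symptoms. It does not rescue the model for the change question: a joint test also rejects when women with more symptoms have higher LEAF-Q scores and nobody's score changes.

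A reader might also infer that the authors expect LEA and symptoms to improve together. No section says so. The article calls LEA a potential modifier and asks only whether it changes and whether this is associated with symptoms.

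The sizes rest on assumed values, and this stands. In the half-tracking case the day term was significant in 89.5% of trials under values A and 25% of cohorts under values C. The robust result is the attenuation, not a particular power.

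Centring, the order of model building and a split of burden into between-woman and within-woman parts may be left to a fuller plan, and the interaction may be a second step. That is fair, and none of these is counted as an error here. The problem already arises from day plus burden.

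Finally, the day-only model is not free of difficulty. Participation ends at full return to work or study, so later records come from slower recoverers. Under values C the day-only slope was -0.39 per week against a mean within-woman slope of -0.51.

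**Conclusion.** The point holds in a limited form. The model named for change over recovery conditions on a covariate that is expected to change with recovery, so its day term targets change at fixed burden. This follows from the stated model and needs no simulation. The understatement is in proportion to the share of the LEA change that tracks symptoms: none if the change is unrelated to symptoms, about half at half tracking, and essentially all of it only at full tracking, where detection drops from 99-100% to about 3-10% under the assumed values.

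The symptom half of Aim 4 is largely intact: where LEA was set to follow burden, the burden term was significant in 83.5-100% of simulated trials. Aim 4 is not the primary aim, and the 30 and 38 women for Aim 1 are unaffected. The change should be made, but the study does not depend on it.

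**What to change.** Answer the two parts of Aim 4 with two models.

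1. **Change over recovery:** a linear mixed model of LEAF-Q score on day, with a participant random effect and without burden. Name its day coefficient as the estimate of change.
2. **Association with symptoms:** add total symptom burden, and then the day-by-burden interaction with burden centred. Describe the day term here as change at a given burden.

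Splitting burden into each woman's mean and her weekly deviation from it is an optional refinement that would separate differences between women from change within a woman.

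The cost is one extra model and a few lines of text, with no new data, visits or participants. Because follow-up ends at return to work or study, the report should say that later records come from slower recoverers and read the day-only slope with that in mind.

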#### Sample size calculation

Using PASS15 software, and a Cox Proportional-Hazards regression model it was estimated that the number of participants needed to examine the primary aim (recovery time in days) is 30. This will allow the detection a hazard ratio of 1.5 (log hazard ratio coefficient = 0.4055), with 80% power, and a type I error rate of 0.05. This was calculated assuming a covariate SD of 1.5, a multiple regression R^2^ (variable of interest regressed on covariates) of 0.2, and an expected event (clinical recovery) rate of 0.9 within the follow-up period. [16, 22] Allowing for 20% drop out during follow-up, 38 participants will be recruited. As of 18 August 2023, 14 eligible women have started the study.

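### Aim 4 reads a joint association of symptom burden and recovery time with LEA from their interaction, which tests only whether the burden-LEA association changes over time (minor)

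*Protocol article*

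**What the plan says.** The protocol article, under Aim, sets Aim 4 as to "investigate whether low energy availability changes across the recovery period, and if this is associated with symptoms experienced".

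Under Data analysis, the method is a linear mixed model for LEA. "This model will incorporate the day of recovery and total symptom burden as fixed effects", and it "will account for repeated measures over time by specifying participant as a random effect". The section continues: "The interaction between symptom burden and recovery time will also be evaluated", and gives the reason as "to understand if these variables are collectively associated with low energy availability". No joint test of the two variables and no centring is described.

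Under Surveys and questions, and in Table 2, the LEAF-Q is first completed seven days after the initial assessment and weekly after that. The symptom scale is also completed at presentation.

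Alpha and power ("with 80% power, and a type I error rate of 0.05") are given under Sample size calculation for Aim 1 only. Strengths and limitations of the study confirms that power rests on the primary aim.

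**The concern.** The sentence names a test and the conclusion to be drawn from it, and the two do not match. A product term asks whether the slope of LEA on burden is the same on every day. Collective association, in its ordinary sense, asks whether burden and day together carry any information about LEA. Two variables can be strongly associated with an outcome, separately and together, with no interaction at all.

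At stake is how a null result is interpreted. If the interaction is not significant, which is what additivity would usually produce, the sentence invites the statement that burden and recovery time are not collectively associated with LEA. The test would not support that.

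There is also a side effect. Once the product term is in the model, each main-effect coefficient is a slope at the zero of the other variable. Uncentred, the burden coefficient refers to day 0, where there are no LEAF-Q data.

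**Working it through.** **The plan's own figure.** Aim 4 has no stated sample size or power. The Aim 1 figure reproduces, which settles the sidedness of the stated alpha:

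N = (1.960 + 0.842)² / (1.5² × 0.4055² × (1 − 0.2) × 0.9) = 7.849 / 0.2664 = 29.47, rounded up to 30. With 20% dropout, 30 / 0.8 = 37.5, rounded up to 38. A one-sided 0.05 would give 24, so the stated alpha is two-sided. Applying 0.05 two-sided to Aim 4 is an assumption.

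**The model.** With D for day, S for burden and u for the participant effect:

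LEA = β0 + β1·D + β2·S + β3·D·S + u + error

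- Interaction null: β3 = 0.
- Joint null: β1 = β2 = β3 = 0 (3 df), or β1 = β2 = 0 in the model without the product (2 df).
- Burden slope on day D: β2 + β3·D. Uncentred, β2 is the slope at D = 0.

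Under additivity β3 is zero, so the interaction test rejects with probability alpha whatever β1 and β2 are. This follows from the algebra and needs no simulation.

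**Simulation, for the other terms.** The protocol gives no LEAF-Q variances, slopes or visit counts, so all of these are assumed:
- 30 women with 1 to 6 weekly records each;
- baseline burden with mean 60 and SD 25, decaying as exp(−day/25), with noise SD 10;
- between-woman SD 3 and residual SD 2, with variance components treated as known;
- Wald tests at two-sided 0.05 and 2,000 replicates (Monte Carlo standard error about 0.5 percentage points at 5%).

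Effects are LEAF-Q points per day, per burden point and per product unit, with day centred at 18 and burden at 30. Cells show percent rejected, uncentred fit / centred fit. The interaction and joint tests do not depend on centring, so their pairs differ only by simulation error.

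| Truth (day, burden, product) | Burden term | Interaction | Joint 3 df | Joint 2 df |
|---|---|---|---|---|
| none | 5.2 / 5.6 | 4.3 / 5.0 | 4.8 / 5.4 | 6.0 / 4.4 |
| 0.03, 0.03, 0 | 24.5 / 33.0 | 5.4 / 5.1 | 24.6 / 25.1 | 28.4 / 29.2 |
| 0.06, 0.08, 0 | 89.2 / 96.6 | 5.0 / 4.6 | 96.0 / 96.0 | 97.8 / 97.4 |
| 0.03, 0.03, 0.001 | 9.9 / 31.8 | 11.6 / 10.9 | 24.2 / 22.1 | 23.1 / 20.8 |
| 0.03, 0.03, 0.003 | 16.2 / 31.6 | 61.7 / 61.4 | 53.0 / 52.8 | 13.6 / 13.9 |
| 0.03, 0.03, 0.005 | 66.3 / 31.7 | 94.8 / 95.4 | 91.0 / 90.6 | 18.4 / 17.0 |

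**Reading the table.**
- In the additive rows the interaction stays near 5% while the joint tests go from 25–29% to 96–98%.
- In the same rows the planned burden term does about as well as the joint tests.
- In the last three rows the uncentred burden slope at day 0 is 0.03 − 18 × product, that is 0.012, −0.024 and −0.060, although the slope at day 18 is +0.03 throughout. The uncentred coefficient shrinks and then changes sign, so its test can mislead either way.

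**The case against.** The strongest reply is that the plan does not leave the association to the interaction. Day and burden are fixed effects, and the product is evaluated in addition. A reader might infer from the 5% figure that Aim 4 would miss a real joint association about 95% of the time. The documents do not support that. The 95% is 1 minus alpha, under a strictly additive truth, with an alpha stated only for Aim 1, and with the interaction as the only test consulted. The planned burden term would show a strong additive association in 89% to 97% of replicates. Where a true interaction exists, the interaction test's own miss rate runs from about 89% to 5%. This part of the reply stands.

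Second, Aim 4 can be read as asking whether the change in LEA is associated with symptoms. That is a time-by-burden question, for which the interaction is a reasonable test. This also stands as a reading, but then the purpose given under Data analysis is still wrong, because the test would answer effect modification.

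Third, no decision rule says that a non-significant interaction will be reported as no association. That is correct: the misreading is a risk that the sentence creates, not a stated intention.

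Fourth, a joint test is no perfect answer either: it can reject when only one of the two variables matters. This stands and shapes the fix.

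Finally, centring and omnibus tests are details that an article may leave to a fuller document. Their absence alone would be no finding. The mismatch between test and stated purpose, however, is in the article's own text.

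**Conclusion.** The point holds as a minor error of inference in a secondary aim. The interaction cannot show whether burden and recovery time are collectively associated with LEA. Under a purely additive association, and an assumed two-sided alpha of 0.05, it rejects about 5% of the time, so a non-significant result says nothing about joint association. That 5% rests on additivity and alpha alone; the other percentages rest on the assumed variances, slopes and visit pattern and are illustrative.

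The main effects already in the model can detect an additive association. What limits them is interpretation: with the product term fitted and the variables uncentred, the burden coefficient is an extrapolation to day 0, a week before the first LEAF-Q. The data collected, the rest of the model and the sample size are unaffected.

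**What to change.** 1. State the interaction's purpose as examining whether the association between symptom burden and LEA changes over recovery.
2. If collective association is a question of interest, answer it with one prespecified joint test: day and burden in the additive model (2 df), or day, burden and their product (3 df). If a likelihood ratio test is used, fit by maximum likelihood. Under additivity the two perform alike; the 3-df test keeps more power when the slope changes with day (53% against 14% in the moderate-interaction row).
3. Report the individual coefficients with confidence intervals beside the joint test, because its rejection does not show which term is responsible.
4. Centre day and burden at values within the observed range, so that each main effect describes a point where LEAF-Q data exist.

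The cost is a reworded sentence and one additional test in a secondary aim. No new data or participants are needed. The joint test does not supply power that the study lacks: under the moderate additive effects above it rejected in only 25% to 29% of replicates.
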